### Recruitment

All pregnant women with asthma attending their first booking visit (approximately 12 weeks gestation) at the antenatal outpatient clinic will be identified by the attending midwife. The midwife will ask several questions to establish the presence of asthma including “have you been told by a doctor that you have asthma? As well as “Have you used any asthma medications in the last year such as salbutamol or a preventer?” Women identified as having asthma will be referred by the attending midwife and will be subsequently interviewed by a research midwife associated with this study who will explain the project to them by providing both written and verbal information.

To be eligible, participants must be less than 20 weeks gestation at the time of recruitment, have asthma which has been previously diagnosed by a doctor and is not currently in remission (remission defined as no asthma symptoms and no use of asthma medications in previous year), aged 18–45 years, expected to give birth to a singleton and be able to speak English. Participants will be excluded from the study if they have previously participated in an Asthma study run at the hospital or have a pre-existing chronic medical condition (i.e. diabetes, hypertension, cardiac disease, HIV/hepatitis, renal disease, haematology disorder (i.e. thalassaemia, thrombophilia), thyroid disorder, psychiatric disease requiring therapy with antidepressant or antipsychotic, epilepsy).

### Data collection at trial entry

Eligible women who agree to take part in the study and sign an informed consent, will be asked to complete a baseline assessment of their asthma. Participants will be asked routine questions to determine their asthma severity in accordance with the National Asthma Council Asthma Management Handbook classifications [12]. This classification takes into account asthma medications, symptoms and spirometry results to reach an approximate baseline asthma severity classification in women with **treated** asthma. Women will be classified as intermittent, mild, moderate or severe. In addition, their asthma control will be assessed by administering the Juniper Asthma Control Questionnaire (ACQ) (how many days in the past week the subject has been affected by night time symptoms, morning symptoms, activity limitation due to asthma as well as frequency of β2-agonist use) [17]. Forced expiratory volume at one second (FEV1) and forced vital capacity (FVC) will be measured by an Easy One spirometer before and after administration of salbutamol in all subjects. FEV1% predicted will be calculated based on the patients age, ethnicity and height using the equations of Gore *et al.*[31]. Further data will be collected using a cold and flu questionnaire to determine the impact of illness on current asthma control. These validated questionnaires, in addition to a structured data collection form, will be used to determine current asthma therapy and control, current asthma triggers and co-morbidity and past history including frequency of oral corticosteroid use and previous hospital admissions for asthma. In addition, data will be collected on smoking (direct and passive exposure), Quality of Life (Mini Asthma Quality of Life Questionnaire [32]) and psychological variables using the Perceived Control of Asthma Questionnaire [33], Brief Illness Perception Questionnaire [34], Medical Adherence Report Scale-Asthma [35], Patient-Clinician Communication Questionnaire [36], Beliefs About Medicines Questionnaire [37], Teratogenic Risk Perception Questionnaire [38], and a purpose designed Asthma Knowledge Questionnaire. For all participants blood will be drawn for total IgE and RAST testing to assess atopy.

### Study groups and management

Eligible women with asthma will be randomized into one of two study groups: either the ‘Standard Care Group’ or the ‘Intervention Group’.

### Randomization

After the baseline assessment of asthma at 18 weeks gestation, women will be randomised to receive either standard care or nurse-led asthma management during pregnancy by contacting the central telephone randomization service at the University of Adelaide. The telephone randomization service will use a randomization schedule with balanced variable blocks, prepared by an investigator not involved with recruitment or clinical care. Stratification will be undertaken according to treatment site, parity and asthma severity. During the randomization call, eligibility will be checked and information collected to enable stratification and to assist in follow-up.

### Treatment schedules

#### Standard care group

Standard care will be as outlined in the SA Perinatal Practice Guideline for the treatment of asthma during pregnancy (Available from http://www.sahealth.sa.gov.au). This involves women with asthma self managing their disease during pregnancy and seeking guidance for asthma management when required from a midwife, obstetrician, respiratory physician or GP. Some women in this group will already be managed by a respiratory specialist and this will be continued. While women receiving standard care will be followed-up at exactly the same time points as those in the intervention group, no formal attentional control will be utilized. Notably, while some researchers advocate for the use of attention controls there is, at this point in time, a significant lack of understanding regarding what constitutes an appropriate attention control group. There is also a lack of understanding regarding the potential benefits (or biases) associated with the use of an attention control, limiting its ability to be utilized in this setting [39].

#### Intervention group

The intervention group will receive care through the nurse-led Antenatal Asthma Management Service, based in the antenatal outpatient clinic. The Antenatal Asthma Management Service will be led by a respiratory nurse with qualifications in asthma management and education and spirometry. The details of the methodology to be used for nurse-led respiratory care in our study have been previously published [17]. All asthmatic women will receive asthma education with a full assessment of their asthma at 18, 24, 30 and 36 weeks gestation conducted by a respiratory nurse. Each antenatal visit will include a 60 min session where asthma management skills are assessed including: medication adherence and knowledge, inhaler device technique, recognition of asthma deterioration and possession of a written asthma action plan [17]. In addition, subjects will receive education about asthma control and management skills including trigger avoidance and smoking cessation counseling when appropriate [17]. While it is standard antenatal care for all pregnant women to complete a smoking questionnaire at their first booking visit and be encouraged to quit smoking, an additional key component of the Antenatal Asthma Management Service will be in providing additional counseling on the importance of smoking cessation in relation to their asthma and the health of their baby. Women will be provided with information on the benefits of smoking cessation and direct referrals will be made to QuitSA for cessation support.

During the first visit at 18 weeks gestation, all subjects will be provided with an individualized written asthma action plan, which has been developed according to evidence based principles by the asthma educator using a standardized template following National Asthma Council recommendations [12]. In addition, current asthma management therapies will be evaluated and recommendations regarding optimal therapy will be made. If women are identified at their first antenatal visit as having unstable asthma, as determined by the Juniper Asthma Control Questionnaire (ACQ) score of >1.5 a recommendation will be made for step-up therapy in accordance with well-established clinical guidelines and previous studies [28]. If inhaled corticosteroids need to be prescribed an on-call respiratory physician will be contacted. A detailed asthma management report, including asthma action plan and recommended changes in therapy if required, will be forwarded to the participant’s preferred family physician (i.e. general practitioner) who will review each action plan and assess the appropriateness of recommended changes in therapy. This preferred provider will be the lead clinician responsible for her asthma management during pregnancy. All recommendations made through the Antenatal Asthma Management Service will be recorded and followed-up to determine their outcome (i.e. acceptance of recommendation).

During subsequent visits to the Antenatal Asthma Management Service, the respiratory nurse will continually review asthma control and management plans. Subjects assessed as having poor asthma control (ACQ > 1.5) or experiencing a current exacerbation will be referred to their usual family physician in the community or respiratory physician in the hospital for appropriate review. During antenatal appointments urgent medical review will be available for patients with an acute exacerbation. The respiratory nurse and designated family physician and/or respiratory physician will collaborate closely on appropriate step-up therapy for the participant.

Between visits, participants will be encouraged to follow their asthma action plan closely and see their family doctor if their asthma worsens. Those subjects who also attend specialist respiratory clinics will also have information forwarded to their physician for reference. Subjects will be encouraged to maintain these specialist visits. During the study, care received for asthma management from a GP, obstetrician or respiratory specialist will be noted.

A flow chart of care is depicted in Figure 1.

**Figure 1 F1:**
[figure not shown]
AAMS study design.

### Data collection

All women will receive a baseline assessment of their asthma as previously described. Data will be collected on participants receiving standard care by a trained research midwife and those receiving the intervention by the respiratory nurse at 24, 30 and 36 weeks gestation. This will be undertaken using a structured data collection tool. At each time point asthma control will be assessed using the ACQ and spirometry. Further data will be collected using a cold and flu questionnaire to determine the impact of illness on current asthma control. A current pregnancy related history will be collected by research midwife interview for any unscheduled doctor visits due to asthma, an increased use of inhaled glucocorticoid, any visits to the Emergency department and any hospital admissions related to asthma, occurring since the previous visit. These data will be used to determine the number and timing of any asthma exacerbations occurring during the study. Data on asthma medication use will be utilized to calculate a cumulative ICS dose for each trimester. In addition, women will be asked to complete a questionnaire relating to smoking (direct and passive), and asthma related quality of life. Furthermore, data will be collected on the level of care received for asthma management from a GP, obstetrician or respiratory specialist (i.e. type and number of visits). Women receiving care through the Antental Asthma Management Service will have additional data collected on psychological variables as outlined in the section on data collection at trial entry (i.e. Perceived Control of Asthma Questionnaire [33]). Medicare Benefits Scheme (MBS) and Pharmaceutical Benefits Scheme (PBS) data relating to medical care and medication use throughout pregnancy will be accessed by participant consent. For all women, data on pregnancy complications, labour, delivery and birth outcomes will be abstracted from delivery case notes.

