### Asthma exacerbations during pregnancy are associated with an adverse outcome

Exacerbations are a key feature of asthma and ideal target for improving asthma control and related outcomes. The definition of an asthma exacerbation is any asthma related event that involved one or more of the following; a hospital admission, an unscheduled doctor visit, a course of oral steroids or an increase in medication use. A systematic review identified that 6% of asthmatic women are hospitalized for a severe exacerbation during pregnancy, and that 20% have a severe exacerbation during pregnancy requiring medical intervention [7]. Furthermore, evidence demonstrates that the rates of exacerbations during pregnancy increases according to asthma severity [18]. Among those with mild, moderate and severe asthma the exacerbation rates have been reported as 13%, 26% and 52%, respectively [18]. The corresponding rates of exacerbations leading to hospitalization were 2%, 7% and 27% [18]. Relying solely on asthma severity, however, can be misleading as asthma can worsen during pregnancy regardless of maternal pre-pregnancy severity [7,10]. That is to say; an asthmatic woman can be a mild asthmatic pre-pregnancy and become a severe asthmatic during pregnancy. In addition, the severity of an exacerbation does not always reflect underlying asthma severity (i.e. women with mild asthma can have a severe exacerbation). This means it is difficult to identify accurately those women at risk of worsening asthma during pregnancy.

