### Outcomes and measures

#### Primary study outcomes

The primary outcomes in this study will be the percentage of women that experienced exacerbations during pregnancy (moderate and severe) defined as events for which the participant sought medical attention (i.e. an unscheduled visit to a doctor, presentation to the emergency department room or admission to hospital, or when oral corticosteroids were used for treatment of asthma). Based on previous research undertaken by our research group it is hypothesised that participation in the Antenatal Asthma Management Service will result in a 20% reduction (absolute) in the incidence of asthma exacerbations during pregnancy in the intervention group compared to the control group [28].

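### The interview items that determine exacerbations do not match the primary outcome definition, and no rule stops actions prompted by the intervention from being scored as events

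*Protocol article*

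**What the plan says.** Three sections of the protocol article list what makes an exacerbation.

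- **Primary study outcomes.** The outcome is the percentage of women with moderate or severe exacerbations, meaning events for which the woman sought medical attention: "an unscheduled visit to a doctor, presentation to the emergency department room or admission to hospital, or when oral corticosteroids were used" to treat asthma. An increase in inhaled steroid is not on this list.
- **Data collection.** At each follow-up the history asks about unscheduled doctor visits for asthma, "an increased use of inhaled glucocorticoid, any visits to the Emergency department and any hospital admissions related to asthma, occurring since the previous visit". The section then says that these data determine the number and timing of any exacerbations. Oral corticosteroid use is not among the items.
- **Background, on exacerbations and adverse outcome.** An exacerbation there is an event involving "a hospital admission, an unscheduled doctor visit, a course of oral steroids or an increase in medication use".

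The Intervention group section describes what the service does. At the first visit, if the ACQ score exceeds 1.5, "a recommendation will be made for step-up therapy". At later visits, "Subjects assessed as having poor asthma control (ACQ > 1.5) or experiencing a current exacerbation will be referred to their usual family physician" or to a hospital respiratory physician. The Standard care group section describes no such prompts; those women manage their own asthma and seek advice when they need it.

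**The concern.** There are two problems. First, the data said to determine exacerbations cannot by themselves reproduce the primary outcome. One qualifying criterion, oral corticosteroid use, has no matching interview item, and one interview item, increased inhaled steroid, has no matching criterion. An oral steroid course that came without a recorded visit could be missed in either arm.

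Second, the item that does not belong is one the intervention is designed to change. A step-up recommended at 18 weeks can be recorded at 24 weeks as increased inhaled steroid since the previous visit. A referral for an ACQ score above 1.5 can produce a doctor visit that an assessor may call unscheduled. The referral rule names poor control and a current exacerbation as alternatives, so the protocol itself allows a referral with no exacerbation. Such entries could arise in the intervention arm because the service did its work and not because asthma worsened. What counts as a primary event would then depend on the arm. If the initiator of a visit and the dates of oral steroid courses are not recorded at the time, this is hard to repair afterwards.

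**Working it through.** **Comparing the lists**

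| Item | Background | Primary study outcomes | Data collection interview |
|---|---|---|---|
| Unscheduled doctor visit | yes | yes | yes |
| Emergency department attendance | not listed | yes | yes |
| Hospital admission | yes | yes | yes |
| Oral corticosteroids | yes | yes | **no** |
| Increased medication or inhaled steroid | yes | **no** | **yes** |

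The last two rows are the mismatch. The article defines neither an unscheduled visit nor how a visit prompted by the service is classified.

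**Illustrating the size**

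Inputs from the Sample size section: 45% of control women and 25% of intervention women with an event; 189 per arm; 15% loss to follow-up. The test is two-sided at 0.05 (Statistical analysis). The evaluable number per arm is 189 × 0.85 = 160.65.

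The plan's own 90% power is not reproduced by these inputs. For 45% against 25%, 90% power needs 118 per arm, or 278 in total after 15% loss, not 378. I therefore take 378 as given and compute the power it yields.

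Let x be the share of otherwise event-free intervention women scored only because of a prompted visit or inhaled steroid increase. The documents give no value, so x is an assumption. Then:

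- observed intervention rate p2 = 0.25 + 0.75x, and difference d = 0.45 − p2
- p̄ = (0.45 + p2)/2
- SE0 = √[2p̄(1 − p̄)/160.65]
- SE1 = √[(0.45 × 0.55 + p2(1 − p2))/160.65]
- power = Φ[(d − 1.96 × SE0)/SE1]

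At x = 0: SE0 = √(2 × 0.35 × 0.65/160.65) = 0.0532 and SE1 = √((0.2475 + 0.1875)/160.65) = 0.0520. Power = Φ[(0.20 − 0.1043)/0.0520] = Φ(1.84) = 97%.

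| x (assumed) | Observed intervention rate | Difference (points) | Pooled power, 15% loss | Pooled power, 5% loss |
|---|---|---|---|---|
| 0 | 25.0% | 20.0 | 97% | 98% |
| 5% | 28.75% | 16.25 | 86% | 89% |
| 10% | 32.5% | 12.5 | 63% | 68% |
| 15% | 36.25% | 8.75 | 36% | 39% |

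The 5% column is shown because the Abstract gives that loss figure. The planned difference would vanish at x = 0.20/0.75 = 26.7%. These are comparisons of two proportions, the form in which the plan states its target effect.

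**The case against.** The strongest reply is that the Primary study outcomes section is the operative definition and is explicit. Read alone, it does not count an inhaled steroid increase, so a step-up by itself creates no primary event. The Background wording introduces literature rates. The interview is said to inform any exacerbations, a wider set, and the Cost effectiveness section needs mild ones too. This is fair: a reader might infer that inhaled steroid increases will be scored as primary events, and the article does not establish that. What remains is that no grading rule is stated, and the only sentence on how exacerbations are determined points to the mismatched list.

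On visits, a nurse referral is arguably neither sought by the participant nor unscheduled. Two assessors could reasonably differ, and no rule settles it.

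On oral steroids, a reader might infer that they go unrecorded. That is not shown either. Medication use is collected, prescription benefit data are accessed with consent, and the structured collection tool is not reproduced. But the only stated use of the medication data is cumulative inhaled steroid dose, and neither source is said to feed the primary outcome.

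Some of the information needed already exists: service recommendations are logged and followed up, and the type and number of asthma care visits are recorded.

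Finally, the hypothesised effect is attributed to an earlier trial in which all women attended a nurse-led service. Prompted contacts may already be reflected in that evidence, which cannot be checked here.

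**Conclusion.** The mismatch between the interview items and the primary outcome is a matter of text and holds without any assumption. The arm-specific mechanism is real but conditional: it operates only if inhaled steroid increases, or visits made on service referral, are scored as primary events. The article neither requires nor prevents this.

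That mechanism pushes against the intervention. It would go too far to conclude that the trial as a whole is biased against the intervention. Missed oral steroid courses could act in either direction. Follow-up data are also said to come from the treating respiratory nurse in one arm and a research midwife in the other, although the exacerbation history itself is assigned to a midwife interview. The net direction is not established.

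The power figures of 86%, 63% and 36% are arithmetically sound but rest wholly on assumed shares of 5%, 10% and 15%. They show that a modest share would matter, not that such a share will occur.

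**What to change.** 1. State that the definition under Primary study outcomes alone determines the primary outcome, and align the Data collection and Background wording with it.
2. Add dated oral corticosteroid courses to the interview in both arms.
3. Keep inhaled steroid increases as a treatment measure only, never as a primary event.
4. Record in both arms who initiated each asthma visit, drawing on the recommendation log and the visit data already collected.
5. Prespecify two sensitivity analyses: one restricted to oral steroid use, emergency attendance or admission, and one that leaves out visits made solely on service referral.

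Do not remove service-referred visits from the primary outcome itself. Such a rule can act in one arm only and would lean on the treating service's records, while a standard-care woman with similar control who sees her doctor unprompted would still count. It could therefore bias in favour of the intervention.

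The cost is one or two form fields, some wording and two extra analyses. The restricted analysis will have fewer events and so less precision. No change to care is involved.

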#### Secondary study outcomes

For the mother, the secondary outcomes will be:

Asthma related variables defined as; ACQ score and FEV1 throughout gestation, asthma related quality of life, perceived control of asthma, medication adherence and asthma knowledge.

Adverse health outcomes defined as; hypertensive disorders of pregnancy, antepartum haemorrhage, gestational diabetes, preterm labour, need for antenatal hospitalization, weight gain during pregnancy, chorioamnionitis requiring antibiotics during labour, length of postnatal hospital stay, use of postnatal antiobitiocs and postpartum haemorrhage (≥500 mls) and emergency caesarean section.

For the infant/child, the secondary study outcomes will be:

Cases of infant morbidity defined as; Gestational age at delivery (determined by date of the last menstrual period and 18 week ultrasound), Preterm delivery (<37 weeks gestation), birth weight, birth length, head circumference IUGR (defined as those babies whose birth weight was less than or equal to the 5th centile), birth-weight-percentile (calculated using http://www.gestation.net), Apgar scores, congenital malformations, admission to neonatal intensive care unit or special care nursery and stillbirth.

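### Three secondary outcomes (perceived control, medication adherence, asthma knowledge) have questionnaire follow-up planned, on the plain reading, in the intervention arm alone, so the arms cannot be compared on them as the analysis section intends

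*Protocol article*

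**What the plan says.** Under Secondary study outcomes, the maternal asthma-related list is ACQ score and FEV1, followed by "asthma related quality of life, perceived control of asthma, medication adherence and asthma knowledge".

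Under Data collection at trial entry, women who consent complete a set that includes "psychological variables using the Perceived Control of Asthma Questionnaire [33], Brief Illness Perception Questionnaire [34], Medical Adherence Report Scale-Asthma [35" and several belief and communication questionnaires, "and a purpose designed Asthma Knowledge Questionnaire". This is before allocation: "After the baseline assessment of asthma at 18 weeks gestation, women will be randomised".

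Under Data collection, the 24, 30 and 36 week visits cover both arms for ACQ, spirometry, the cold and flu questionnaire, exacerbation history, medication use, smoking, quality of life and care received. The section then says: "Women receiving care through the Antental Asthma Management Service will have additional data collected on psychological variables". It identifies these variables by pointing back to the baseline set, and the one instrument that it names is the perceived-control questionnaire.

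Under Standard care group, "women receiving standard care will be followed-up at exactly the same time points as those in the intervention group". No instruments are named there.

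Under Statistical analysis, outcomes are compared by randomised allocation. Repeated questionnaire scores go into a mixed model with a random intercept, and sub-analyses examine the effects of knowledge and adherence, among other variables, on the outcomes.

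**The concern.** An outcome listed for a randomised comparison has to be measured after randomisation in both arms. Here the collection rule and the outcome list disagree for three outcomes.

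These three are the nearest effects of a service made up largely of education and self-management support. If exacerbations fall, or fail to fall, they would help show whether the service changed what women know, believe and do. With follow-up in one arm, the available result is change from baseline in treated women. That change mixes any effect of the service with learning from repeated testing, regression to the mean and the course of pregnancy. A statistical analysis plan cannot repair this later, because the control data would never have been collected.

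**Working it through.** The plan gives no figure for these outcomes, so there is none to reproduce. The check is a comparison of sections, followed by what can be estimated.

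**Step 1. Where each asthma-related secondary outcome is measured after baseline**

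| Outcome | Instrument | Intervention arm | Standard care arm |
|---|---|---|---|
| Asthma control | ACQ | yes | yes |
| FEV1 | spirometry | yes | yes |
| Quality of life | asthma quality-of-life questionnaire | yes | yes |
| Perceived control | Perceived Control of Asthma Questionnaire | yes, named | not provided for |
| Adherence | Medical Adherence Report Scale-Asthma | yes, by reference to the trial-entry set | not provided for on this scale |
| Knowledge | Asthma Knowledge Questionnaire | yes, by reference to the trial-entry set | not provided for |

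So 3 of 6 asthma-related outcomes are affected. The whole secondary list has 6 asthma-related, 11 other maternal and 11 infant items, 28 in all, so the share of that list is 3/28, about 11%.

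**Step 2. Numbers available.** The Sample size section gives 189 women per group. Follow-up scores on these instruments would come from at most 189 intervention women and 0 standard-care women.

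**Step 3. What the mixed model can estimate.** For woman i at visit t, write

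Y_it = b0 + b1·(after baseline) + b2·(after baseline × intervention) + u_i + e_it.

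Baseline scores in both arms inform b0. Every post-baseline score comes from an intervention woman, so b1 and b2 enter only as the sum b1 + b2. The effect of the service is b2, and it cannot be separated from the time trend b1. Treating the control scores as missing at random does not help, because no control has an observed follow-up score from which to learn.

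**Step 4. Sub-analyses of knowledge and adherence.** Baseline values exist for women in both arms and precede randomisation, so a both-arm analysis using them is possible. One using follow-up questionnaire values is not.

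**Step 5. What both-arm follow-up would offer.** The detectable standardised difference, two-sided 0.05, unadjusted, is (1.96 + z_power) × √(2/n).

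- 15% loss (Sample size section): 189 × 0.85 = 160.65, so n = 160 per arm. The result is 0.36 SD at 90% power and 0.31 SD at 80%.
- 5% loss (Abstract): 189 × 0.95 = 179.55, so n = 179 per arm. The result is 0.34 SD at 90% power and 0.30 SD at 80%.

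The planned sample would therefore support a useful comparison.

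**The case against.** Several objections carry weight.

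- **Exclusion of controls is inferred.** The article does not state that standard-care women are not given the questionnaires. The study design figure is not available to check, and a condensed article may leave a visit-by-instrument schedule to the full protocol. A reader might infer an express decision to leave controls out; the text does not support that. Even so, data described as additional, given to one named arm straight after a list for all women, have one natural meaning, and no other section contradicts it. The shared time points in Standard care group settle when controls are seen, not what they complete.
- **The cross-reference names only perceived control.** Read strictly, adherence and knowledge would have no stated follow-up questionnaire in either arm, only assessment within the nurse sessions described under Intervention group. That reading does not restore a between-arm comparison.
- **Adherence is not wholly unmeasured in controls.** A reader might infer that there are no control data at all. That is too strong: medication use is recorded and pharmaceutical-claims data are sought by consent, with no restriction to one arm. They could give a proxy, but the protocol does not define the adherence outcome that way, and they say nothing about knowledge or perceived control.
- **The analysis section is not proof of intent for each scale.** Its mixed-model sentence is satisfied by ACQ and quality of life, which both arms complete. The sub-analyses could rest on baseline values, so it would be wrong to call them invalid.
- **Measuring controls may change them.** Repeated questions on adherence and knowledge could prompt self-management in a group deliberately left without an attention control. The size of any such effect cannot be judged from the document.

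**Conclusion.** The inconsistency between the outcome list and the collection rule stands. As written, perceived control and knowledge have no post-baseline control data, and adherence has none on its named scale. The comparison by allocation cannot be made on these instruments; only before-after change in the intervention arm is available. Both-arm sub-analyses of knowledge and adherence are limited to baseline values.

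This rests on the plain reading of the Data collection section, and on the Medical Adherence Report Scale-Asthma being the intended adherence measure.

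The point should be fixed, but it does not threaten the trial's main conclusions, and a reader should not infer that it does. The primary outcome, ACQ, FEV1, quality of life and the perinatal outcomes do not depend on these questionnaires. The stated aim is clinical and cost effectiveness, not a test of how the education works.

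**What to change.** Preferred: amend Data collection so that both arms complete the perceived-control, adherence and knowledge questionnaires at 24, 30 and 36 weeks, or at least at 36 weeks, and compare arms adjusting for the baseline score. No new visits are needed. The cost is a few minutes of questionnaire time per standard-care visit, a small amendment, and a possible small reactivity effect in controls, who already complete the same forms at baseline. Collecting them once, at 36 weeks, limits that effect. Because the nurse who delivers the education also collects the intervention arm's data, having women complete the forms themselves in both arms would make the answers more comparable.

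Alternative: remove the three from the secondary outcomes and report them as uncontrolled intervention-arm process measures. This is a wording change, at the price of any randomised evidence on them.

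If both arms were always meant to complete them, correct the Data collection sentence. In every case, state whether the knowledge and adherence sub-analyses use baseline or follow-up values, and whether adherence means the self-report scale or a measure built from medication-use records.
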